# The Chinese herbal formula pediatric Anshen Bunao Granules for the treatment of tic disorder: study protocol for a randomized, double-blind, active-controlled trial

**DOI:** 10.3389/fneur.2026.1822528

**Published:** 2026-05-19

**Keywords:** Chinese herbal medicine, hospital-prepared traditional Chinese medicine formulation, pediatric Anshen Bunao Granules, randomized controlled trial, tic disorder, Tourette syndrome

## Abstract

**Background:**

Tic disorder (TD) affects 2.68% of children in China. It is classified as a movement disorder, with dysfunction in cortical–striatal–thalamic–cortical circuits implicated in its pathophysiology. Western medical treatments for TD may be associated with adverse reactions and suboptimal adherence in some patients. Pediatric Anshen Bunao Granules (PABG) is an in-house traditional Chinese medicine (TCM) preparation with over 20 years of clinical use for TD, approved by the Guangdong Provincial Drug Administration for use in medical institutions across Guangdong Province. Observational studies have reported effects of PABG; however, high-level evidence remains lacking. This study aims to evaluate the efficacy and safety of PABG in children with TD.

**Methods:**

This is a randomized, double-blind, active-controlled, parallel-group trial. A total of 150 children aged 4–16 years with TD (TCM syndrome: Spleen Deficiency with Phlegm Accumulation and Wind-Phlegm Disturbance Syndrome) will be recruited from Shenzhen Traditional Chinese Medicine Hospital, Guangdong Province, China. Eligible participants will be stratified by age group and baseline Yale Global Tic Severity Scale (YGTSS) total score, and randomly allocated at a ratio of 2:2:1 to the low-dose PABG group, high-dose PABG group, or active control group (receiving 5% of the active ingredients to maintain blinding) for 8 consecutive weeks of treatment. Primary outcomes will be the change in YGTSS Total Tic Score (YGTSS-TTS) from baseline to Week 8, and the proportion of participants with a ≥ 30% reduction in YGTSS-TTS at Week 8. Secondary outcomes will be assessed using the YGTSS, the TCM Syndrome Rating Scale (TCM-SRS), and the Gilles de la Tourette Syndrome-Quality of Life Scale for Children and Adolescents (C&A-GTS-QoL). Safety assessments will include vital signs, physical examination, laboratory tests, ECG, and adverse events.

**Discussion:**

This trial will provide evidence on the efficacy and safety of PABG for children with TD. The findings may inform clinical application and potential registration of this in-house TCM preparation.

**Clinical trial registration:**

https://itmctr.ccebtcm.org.cn/, ITMCTR2025001659.

## Introduction

1

Tic disorder (TD) is a neuropsychiatric condition primarily manifesting as rapid and involuntary motor and/or vocal tics, typically emerging during childhood and adolescence (1). It frequently co-occurs with multiple mental and/or behavioral disorders, such as Attention Deficit Hyperactivity Disorder (ADHD), Obsessive-Compulsive Behavioral /Disorder (OCB/OCD), anxiety disorders, depressive disorders, and sleep disorders (2). Motor tics manifest as involuntary muscle contractions, whereas vocal tics present as abnormal vocalizations; certain triggers, such as emotional fluctuations or dietary irregularities, may exacerbate symptoms. According to the diagnostic criteria of the Diagnostic and Statistical Manual of Mental Disorders, Fifth Edition (DSM-5) (3), TD is categorized into three types: transient tic disorder (TTD), chronic motor or vocal tic disorder (CTD), and Tourette syndrome (TS). The mean age at onset for TD is 5 years, with peak symptom severity occurring between 8 and 12 years of age (4). A 2022 study by Jafari et al. (5) indicated a global prevalence of TS of 0.5%. Research published in 2023 indicates an overall TD prevalence of 2.68% in China (6), with males exhibiting a higher incidence of severe symptoms than females (7). Tics can impair patients’ daily functional activities, leading to social isolation, interpersonal conflicts, peer bullying, and disruption to academic or occupational pursuits, thereby diminishing quality of life and adversely affecting the healthy development of personality and psychological well-being (8).

The precise etiology and pathogenesis of TD are widely recognized as involving multifactorial mechanisms, including neurotransmitter dysregulation, genetics, immunological factors, trace element imbalances, and socio-environmental and psychological influences (9, 10). Recent evidence using the 2D:4D digit ratio, a marker of fetal sex hormone exposure, has also suggested a link between these hormone levels and tic disorder (11). Among these, dysfunction within cortical–striatal–thalamic–cortical (CSTC) circuits has emerged as a key neurobiological substrate underlying the pathophysiology of tic disorders (12, 13). The proposed mechanism involves aberrant neuronal firing in the striatum, which disrupts its inhibitory output to the thalamus. Loss of this inhibition allows increased thalamic drive to the sensorimotor cortex, resulting in excessive cortical excitability that produces motor and vocal tics (14, 15). Regarding the treatment of pediatric TD, guidelines issued by the European Society for the Study of Tic Disorders (ESSTS) and the American Academy of Neurology (AAN) recommend psychological interventions and/or pharmacological treatment (16–18). The antipsychotic drug aripiprazole is the most commonly prescribed medication in European clinical practice and has been shown to effectively improve tic symptoms (19). Commonly used antipsychotic drugs include central *α*-adrenergic receptor agonists, selective 5-hydroxytryptamine reuptake inhibitors, and dopamine receptor antagonists. While these medications can alleviate tic symptoms, they present challenges such as a slow onset of action, prolonged treatment duration, multiple adverse effects, and high relapse rates. Certain drugs may suppress normal central nervous system excitability, leading to reduced medication adherence among children and parents (20, 21).

TD treatment necessitates the exploration of additional safe and effective therapeutic approaches to enhance children’s quality of life. Modern clinical practice in traditional Chinese medicine (TCM) (22) demonstrates its advantages in syndrome differentiation–based treatment for childhood TD: it effectively alleviates tic symptoms and comorbidities, reduces recurrence rates, and is associated with fewer adverse reactions. In addition, herbal formulations, such as 5-ling Granules and Ningdong Granules, have been included in the list of compounds with moderate-certainty evidence of therapeutic efficacy (19). Consequently, TCM has emerged as a complementary clinical treatment option for childhood TD (23). TCM possesses millennia of accumulated clinical experience regarding the understanding and management of childhood TD, attributing its onset to factors such as the child’s emotional state and nutritional status (24, 25). Based on fundamental TCM theory, TD can be categorized into several syndromes, with the following four being the most common in clinical practice: Qi Stagnation Transforming into Fire Syndrome, Spleen Deficiency with Phlegm Accumulation and Wind-Phlegm Disturbance Syndrome (SDPWS), Spleen Deficiency with Liver Hyperactivity Syndrome, and Yin Deficiency Stirring Wind Syndrome (26). SDPWS is the most common pattern, accounting for nearly half of the cases (27). Clinically, SDPWS typically presents with motor tics (e.g., eye blinking, head nodding, shoulder shrugging) along with signs of spleen deficiency (e.g., poor appetite, sallow complexion, restless sleep). In contrast, the other patterns show distinct features: Qi Stagnation Transforming into Fire Syndrome is characterized by forceful, frequent tics, irritability, and red face; Spleen Deficiency with Liver Hyperactivity Syndrome presents with weak, intermittent tics, fatigue, and chest distension; Yin Deficiency Stirring Wind Syndrome manifests as chronic, low-intensity tics, night restlessness, and dry stools.

Pediatric Anshen Bunao Granules (PABG) is a pediatric traditional Chinese medicine formulation developed by Shenzhen Hospital of Traditional Chinese Medicine, Guangdong Province, China. Its formula is derived from a modification of Ditan Decoction, a classic phlegm-resolving TCM formula. Registered as an in-house TCM preparation at Shenzhen Hospital of Traditional Chinese Medicine in 2001, it was approved by the Guangdong Provincial Drug Administration for clinical use within medical institutions across Guangdong Province. Over the past 5 years, cumulative usage has reached 64,000 boxes (10 boxes per course), serving over 6,400 pediatric patients. Preliminary pharmacodynamic studies indicate that PABG exhibits antioxidant properties, protects against neuronal damage, and exerts neurotrophic effects (28). A small-scale clinical trial utilized PABG as the intervention and haloperidol tablets (a second-line treatment for TD [29]) as the control; efficacy was assessed using the Yale Global Tic Severity Scale (YGTSS). Results demonstrated that after 6 months of treatment, the PABG group exhibited superior overall and long-term efficacy compared to the control group, alongside a lower disease recurrence rate (29). This formulation comprises 18 Chinese medicinal ingredients, including Acorus tatarinowii, Arisaema cum bile, Polygalae radix, Lapis chloriti, Astragali radix, Pinellia ternata, Poria cocos, Citri reticulatae pericarpium, Haliotidis concha, Notopterygii rhizoma et radix, Corni fructus, Alpiniae oxyphyllae fructus, Aurantii fructus, Fructus tritici levis, Hordei fructus germinatus, Massa Medicata Fermentata, Crataegi fructus, and Glycyrrhizae radix et rhizoma.

Current pharmacological research indicates that multiple herbs in the formulation possess distinct neuropsychiatric–related therapeutic effects: Acorus tatarinowii modulates synaptic plasticity by regulating dopaminergic and glutamatergic neurotransmission, thereby potentially intervening in TD (30); Arisaema cum bile inhibits neuroinflammation and modulates the farnesoid X receptor (FXR) and gamma-aminobutyric acid (GABA) signaling pathways, thereby alleviating convulsions triggered by febrile seizures (31); Polygalae radix has been reported to exhibit sedative, antioxidant, anti-neuroinflammatory, and neuroprotective effects (32); Lapis chloriti has been traditionally employed to relieve epileptic symptoms (33); and Astragali radix possesses anti-inflammatory, antioxidant, and neuroprotective properties (34). Convulsions constitute a core clinical manifestation of TD, sharing common pathophysiological mechanisms with febrile seizures and epilepsy; sedative and neuroprotective actions are closely associated with the regulation of TD symptoms. Furthermore, although the pathogenesis of TD remains incompletely understood, research suggests that neuroinflammation and oxidative stress may contribute to its pathological process (35, 36). The anti-inflammatory and antioxidant properties of Astragali radix may offer potential therapeutic relevance for TD management. The experimental evidence for these Chinese medicinal herbs provides direct or indirect mechanistic support for the clinical application of PABG in alleviating childhood TD symptoms.

In recent years, the National Medical Products Administration of China (NMPA) has introduced multiple policies and regulations encouraging the inheritance and innovative development of TCM. For instance, Article 24 of the Special Provisions on the Registration Management of Traditional Chinese Medicines stipulates that, when conducting the clinical development of TCM with established human experience, real-world evidence may be used as one of the supporting bases for product market authorization under specific conditions. This study, guided by documents such as the Classification of Traditional Chinese Medicine Registration and Requirements for Submission Materials (37) issued by the NMPA in 2020 and the Technical Guidelines for Clinical Trial Design and Evaluation of Traditional Chinese Medicine for Tic Disorders (2021 Edition) (38) published by the Clinical Pharmacology Branch of the Chinese Association of Chinese Medicine (CACM), proposes to conduct a clinical trial of PABG. This trial will generate evidence to support the design of subsequent confirmatory trials and facilitate potential market authorization of this in-house TCM preparation.

## Methods

2

### Aim

2.1

This randomized controlled trial (RCT) aims to evaluate the efficacy and safety of two dose levels of PABG (low and high) compared with a minimal-dose active control (5% PABG). The dose-gradient design allows for exploratory assessment of the dose–response relationship to inform future dose selection.

### Setting

2.2

This is a randomized, double-blind, active-controlled, parallel-group clinical trial. It will be conducted at Shenzhen Traditional Chinese Medicine Hospital. The trial’s design and conduction will adhere to the Declaration of Helsinki and have been approved by the ethics committees at Shenzhen Traditional Chinese Medicine Hospital (No. K2025-111-02). The trial was registered at International Traditional Medicine Clinical Trial Registry (No. ITMCTR2025001659) on 3 September 2025.

### Recruitment

2.3

A total of 150 participants will be recruited from Shenzhen Traditional Chinese Medicine Hospital.

### Inclusion criteria

2.4

Participants must meet all of the following criteria to be eligible for enrollment:

Following the exclusion of other potential diseases via electroencephalogram, psychological testing, and laboratory assessments, a diagnosis of Transient Tic Disorder (TTD), Chronic Tic Disorder (CTD), or Tourette Syndrome (TS) is confirmed according to the tic disorder diagnostic criteria in the Diagnostic and Statistical Manual of Mental Disorders, Fifth Edition (DSM-5) (American Psychiatric Association, 2013) (3).The traditional Chinese medicine (TCM) syndrome differentiation is characterized as Spleen Deficiency with Phlegm Accumulation and Wind-Phlegm Disturbance Syndrome (SDPWS) (Table 1).Aged 4–16 years (inclusive), regardless of gender.A total score of ≥ 25 on the Yale Global Tic Severity Scale (YGTSS).For participants aged ≥ 8 years, the ICF must be jointly signed by the participant and their legal guardian; for participants aged < 8 years, the ICF must be signed by the legal guardian alone.

**Table 1 tab1:** Diagnostic criteria for SDPWS.

Symptom type	Symptoms
Main symptom	(1) Frown and wink; (2) Open mouth and grin; (3) Shake head and shrug shoulders; (4) Shake hands and kick legs; (5) Utter foul language
Secondary symptom	(1) Irritability; (2) Poor sleep quality; (3) Sallow complexion; (4) Dark periorbital discoloration; (5) Sticky or dry stools

The diagnostic criteria are formulated based on the official guidelines issued by the Pediatric Branch of the Chinese Association of Chinese Medicine (2013). Syndrome differentiation is confirmed if a participant presents at least one main symptom plus two to three secondary symptoms. Tongue and pulse manifestations are regarded as supplementary reference indicators.

### Exclusion criteria

2.5

Participants will be excluded if they meet any of the following:

TTD with a disease course ≤ 90 days (TTD with a course > 90 days is eligible).Involuntary movements attributable to other conditions (e.g., rheumatic chorea, Huntington’s disease, Wilson’s disease, choreoathetosis, myoclonus, acute motor disorders, hysterical spasms, epilepsy, drug-induced extrapyramidal disorders, substance/drug-induced motor or muscle tone disorders).Comorbidities including Attention Deficit Hyperactivity Disorder (ADHD), Obsessive-Compulsive Behavior/Disorder (OCB/OCD), learning disorders, sleep disorders, mood disorders, or self-injurious behavior.Confirmed diagnosis of depression or schizophrenia at screening.Use of medications indicated for tic disorder (TD) treatment (or effective for tics) within 14 days prior to randomization (e.g., haloperidol, Jiuwei Xifeng Granules).History of adequate, standardized treatment with ≥ 2 anti-TD drugs (different mechanisms of action) for > 1 year, with no significant efficacy and persistent symptoms.Current receipt of behavioral therapy (eligible after a washout period).Participation (current or past 90 days) in other drug clinical trials, or within 5 half-lives of the study drug (whichever is longer).Hypersensitivity to the study drug or its excipients.Severe comorbidities (heart, brain, liver, kidney, or hematopoietic system); or serum levels of aspartate aminotransferase (AST)/alanine aminotransferase (ALT) > 2.5 × upper limit of normal (ULN); or alkaline phosphatase (ALP)/total bilirubin > 2 × ULN; or clinically significant electrocardiogram (ECG) abnormalities (per investigator assessment).Other conditions deemed unsuitable for enrollment (per investigator judgment).

### Trial design

2.6

This study will comprise three phases as detailed below:

Screening period (W-2 to W0): Participants and their legal guardians will enter the screening phase after signing the Informed Consent Form (ICF), which has been approved by the Medical Ethics Committee of Shenzhen Traditional Chinese Medicine Hospital. Investigators will provide detailed explanations of the study objectives, treatment methods, procedures, potential benefits, and risks, as well as guidance on medication administration and lifestyle precautions during the study period.Treatment period (W1–W8): On Day −1 (D-1), participants who meet all inclusion criteria and none of the exclusion criteria will undergo final eligibility confirmation. Baseline assessments will be performed, including the YGTSS, TCM Syndrome Rating Scale (TCM-SRS), Gilles de la Tourette Syndrome–Quality of Life Scale for Children and Adolescents (C&A-GTS-QoL), and safety evaluations. Eligible participants will then be allocated to the low-dose PABG group, high-dose PABG group, or active control group (containing 5% of the active ingredients for blinding) in a 2:2:1 ratio using stratified block randomization with age and disease severity as stratification factors. According to their group assignment and age, participants will receive the corresponding dosage of PABG or active control, three times daily for 8 consecutive weeks. The detailed dosage regimen is presented in Figure 1. Investigators will conduct follow-up visits at Weeks 2, 4, 6, and 8 after treatment initiation (±2 days permitted). Participants and their legal guardians will document symptom episodes and complete efficacy assessments and safety examinations in accordance with the protocol.Follow-up Period (W12): Participants will return to the study center 4 weeks after the end of treatment (±2 days permitted), at which point investigators will collect efficacy and safety evaluation data.

**Figure 1 fig1:**
[figure not shown]
Dosage and administration regimen of PABG and active control according to age groups and treatment groups.

The trial flow diagram is illustrated in Figure 2.

**Figure 2 fig2:**
[figure not shown]
The flowchart of the trial.

### Sample size

2.7

To date, no active-controlled trial has evaluated PABG for the treatment of tic disorders with SDPWS. The primary endpoint of this study is the change from baseline in the YGTSS–Tic Severity Score (YGTSS-TTS) at Week 8. Preliminary data from our pilot study indicated a mean baseline YGTSS-TTS score of 22.8. The minimal clinically important difference (MCID) for the YGTSS-TTS is defined as a ≥ 25% reduction from baseline (39), corresponding to 5.7 points. Based on effect sizes reported in clinical trials of comparable Chinese patent medicines for tic disorders (40), and considering the dose-gradient design of the present study, we assume a mean reduction of 8.2 ± 7.0 points in the active control group, 12.4 ± 6.8 points in the low-dose group, and 12.9 ± 6.6 points in the high-dose group.

With a two-sided significance level of *α* = 0.025 (Bonferroni correction for two comparisons: high-dose vs. active control and low-dose vs. active control) and *β* = 0.20 (80% power), and an allocation ratio of 2:2:1, the sample size was calculated using PASS version 20.0 (NCSS, LLC, Kaysville, UT, USA). Allowing for a 15% dropout rate, the adjusted and rounded total sample size was determined to be 150 participants, with 60 in the high-dose group, 60 in the low-dose group, and 30 in the active control group. The primary comparisons are each active dose versus the active control; the sample size was not powered to detect a statistically significant difference between the two active doses. The close projected outcomes (0.5-point difference) reflect a conservative assumption, and the dose–response assessment is exploratory.

The assumed effect size between each active dose and the active control (approximately 4.2 to 4.7 points) is consistent with the effect observed in a previous trial of a similar Chinese patent medicine (40), where the active product showed a 4.8 point greater reduction in YGTSS-TTS compared with placebo at week 8. Although this effect is slightly below the MCID of 5.7 points, as an exploratory dose-finding trial, any statistically significant signal, even if below the MCID, would support further investigation in a larger confirmatory trial. The MCID will be used for clinical interpretation of the final results.

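### The inputs in Section 2.7 do not give 150 children at 80% power: unadjusted, 150 gives about 59% for the low dose and 72% for the high dose

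*Protocol article*

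**What the plan says.** Every input is in Section 2.7 (Sample size) of the protocol article.

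- Control effect: "we assume a mean reduction of 8.2 ± 7.0 points in the active control group".
- Dose effects: the low dose is put at a reduction of 12.4 (SD 6.8) and the high dose at 12.9 (SD 6.6). The differences from control are therefore 4.2 and 4.7 points.
- Error rate: "With a two-sided significance level of *α* = 0.025 (Bonferroni correction for two comparisons" of high dose and low dose with control.
- Power and allocation: "0.20 (80% power), and an allocation ratio of 2:2:1".
- Result: "Allowing for a 15% dropout rate, the adjusted and rounded total sample size was determined to be 150 participants", split 60/60/30.
- Scope: "The primary comparisons are each active dose versus the active control". Only the comparison between the two doses is excluded from the powering.

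Section 4.1 plans ANCOVA with baseline and the stratification factors. Section 2.7 uses no covariate correlation, and it does not define power as success on at least one dose.

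**The concern.** A total that is said to deliver 80% power should be recoverable from the effects, SDs, alpha, allocation and dropout printed beside it. This one is not, and the gap is too large for rounding.

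The consequence is greatest for the low dose. If its true effect is the planned 4.2 points, an unadjusted comparison misses it about 4 times in 10 (1 − 0.594 = 0.406), against the 2 in 10 that the text implies. Section 2.1 says the design is meant to inform future dose selection. A reader who trusts the 80% would give a non-significant low-dose result more weight than it can bear.

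**Working it through.** **Inputs** (all from Section 2.7): control 8.2, SD 7.0; low dose 12.4, SD 6.8; high dose 12.9, SD 6.6; two-sided alpha 0.025; power 0.80; each dose against control at 2:1; dropout 15%.

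**Step 1. Try to reproduce 150.** With n control children and 2n on a dose, the normal approximation is n = (z₁₋α/₂ + z₁₋β)² × (SD_c² + SD_t²/2) / d². Here (2.241 + 0.842)² = 9.505.

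- Low dose: 9.505 × (49 + 23.12) / 4.2² = 38.9, so 39 control. Three arms: 5 × 39 = 195 evaluable. 195 / 0.85 = 229.4, about 230 randomised.
- High dose: 9.505 × (49 + 21.78) / 4.7² = 30.5, so 31 control. Three arms: 155 evaluable. 155 / 0.85 = 182.4, about 183 randomised.

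The pooled t test (noncentral t) also gives 39 and 31. Multiplying by 1.15 instead of dividing by 0.85 gives about 225 and 180, so the dropout formula does not explain the gap.

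**Step 2. Power at 150.** After 15% loss there are about 51 per dose and 25.5 control.

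- Low dose: pooled SD = √[(50 × 6.8² + 24.5 × 7.0²) / 74.5] = 6.87. SE = 6.87 × √(1/51 + 1/25.5) = 1.665. Noncentrality = 4.2 / 1.665 = 2.52 against a critical t of 2.288. **Power 59.4%.**
- High dose: pooled SD 6.73, SE 1.633, noncentrality 4.7 / 1.633 = 2.88. **Power 72.2%.**

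| Unadjusted, two-sided 0.025 | Low | High |
|---|---|---|
| Pooled t, 51 v 25.5 | 59.4% | 72.2% |
| Normal approximation, 51 v 25.5 | 60.1% | 71.9% |
| Welch t, 51 v 25.5 | 57.5% | 69.3% |
| Pooled t, no dropout, 60 v 30 | 67.5% | 79.8% |

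**Step 3. Detectable difference.** At 51 v 25.5, 80% power needs a noncentrality of about 3.136. That is 3.136 × 1.665 = 5.2 points (low) and 3.136 × 1.633 = 5.1 points (high).

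**Step 4. Both doses together.** In simulated trials with 25/51/51 evaluable and error pooled over three arms, power for at least one dose is about 79% and for both about 54%. Pooling error pairwise gives 78% and 52%.

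**Step 5. What does give about 150.** Each route contradicts something in the text.

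- High dose at two-sided 0.05: 25 control by pooled t (125 evaluable, 125 / 0.85 = 147) or 26 by normal approximation (130 evaluable, 153).
- Low dose at one-sided 0.05: 26 control, 130 evaluable, 153 randomised.
- High dose at the stated 0.025 with dropout ignored: 31 control, 155 in total; 60 v 30 gives 79.8%.

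**Step 6. What ANCOVA could recover.** This step assumes that the stated SDs are unadjusted change-score SDs. A correlation R with the covariates then multiplies them by √(1 − R²). R = 0.6 (factor 0.80) brings the low dose to 80.4%. R = 0.4 (factor 0.917) brings the high dose to 80.1%.

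**The case against.** **The planned test is ANCOVA, not an unadjusted t test.** This stands as a limit on the claim. The 59% and 72% describe the unadjusted comparison, and adjustment could restore 80%. It does not rescue the stated figure, because the protocol gives no correlation. A reader might infer that the trial lacks 80% power under any analysis; the documents do not support that.

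**The trial is exploratory, and one positive dose would be enough.** Section 2.7 does call it an exploratory dose-finding trial, and power for at least one dose is close to 80%. But the section does not define power that way. It names each dose against control as primary and splits alpha between them. Section 5.1 adds that positive results could support registration.

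**Section 4 uses a two-sided 0.05 threshold.** At that level, power after dropout is about 70% (low) and 81% (high). The low dose still falls short, and the threshold conflicts with the 0.025 of Section 2.7.

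**The error can be diagnosed.** A reader might infer that the Bonferroni alpha was entered one-sided or not applied, and that the low dose was ignored. Step 5 shows why this cannot be concluded: one route to 150 powers the low dose, and another keeps the Bonferroni alpha.

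**A null low-dose result need not be misread.** This is fair. No section says how such a result would be interpreted. The risk is a reason to state the interpretation in advance, not an established consequence.

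**Conclusion.** The point holds. The stated total and the stated 80% power are inconsistent with the other inputs in Section 2.7. On those inputs, 150 randomised children give about 59% power for the low dose and 72% for the high dose; 80% would take about 230 and 183. The low dose falls short even if no child is lost, and the choice among standard formulas moves the power figures by no more than about 3 percentage points.

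This rests on three readings: the stated SDs are unadjusted, dropout falls equally on all arms, and lost children contribute no information. A stated covariate correlation, or a definition of power as success on at least one dose, would change the assessment; the document contains neither. The reason for the discrepancy cannot be established from it.

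**What to change.** Keep 150 and correct Section 2.7. Suggested wording: *With 150 randomised (about 51/51/25 evaluable after 15% dropout) and two-sided alpha 0.025 per comparison, unadjusted power is about 59% for the low dose (4.2 points) and 72% for the high dose (4.7 points). The differences detectable with 80% power are about 5.2 and 5.1 points.*

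If 80% was calculated for the adjusted analysis, state and justify the covariate correlation instead. About 0.6 is needed for the low dose and about 0.4 for the high dose.

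In either case, state in advance that a non-significant low-dose result is inconclusive, and reconcile the 0.025 of Section 2.7 with the 0.05 of Section 4.

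Optionally, replace Bonferroni by Holm across the two dose comparisons on the change endpoint. In simulation this raises power to about 68% (low) and 75% (high) with the same family-wise error over those two tests. It does not restore 80%, and it does not cover the second primary endpoint, the proportion with at least a 30% reduction. Bonferroni is valid, so this is a choice and not a correction.

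The cost is a rewording and a less favourable stated power, with no additional children.

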### Randomization and blinding

2.10

A stratified block randomization sequence will be constructed using SAS software (version 9.4 or later; SAS Institute Inc., Cary, USA) by a team of randomization statisticians. The stratification is based on two factors: age categories (≥4 to ≤6 years, >6 to ≤10 years, >10 to ≤16 years) and baseline disease severity (YGTSS total score ≥25 to ≤50, >50).

All eligible participants will be randomly allocated to the high-dose PABG group, low-dose PABG group, or active control group at a 2:2:1 ratio via the Interactive Web Response System (IWRS). Authorized investigators will access the system to retrieve the participants’ treatment assignments for randomization. The outcomes of the randomization process will be strictly kept confidential.

Neither the participants nor the research team will be informed of the treatment assignments until the conclusion of the study. Emergency unblinding will be carried out through the IWRS in scenarios such as severe deterioration of participants’ conditions requiring emergency rescue or as mandated by regulatory authorities. The rationale, date, and time of unblinding will be documented in the electronic Case Report Form (eCRF), and the relevant participants will be classified as dropouts.

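### Both primary comparisons rest on the smallest arm, and no planned contrast with control uses all 120 PABG children: add one supportive average-dose contrast and restate the power in section 2.7

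*Protocol article*

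**What the plan says.** All references are to the protocol article.

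- Section 2.7 (Sample size) fixes the arms: "with 60 in the high-dose group, 60 in the low-dose group, and 30 in the active control group". Section 2.10 (Randomization and blinding) repeats the 2:2:1 ratio.
- Section 2.7 names the tests: "The primary comparisons are each active dose versus the active control; the sample size was not powered to detect a statistically significant difference" (meaning high dose against low dose). Each test has a two-sided alpha of 0.025 by Bonferroni, with a target power of 80% and 15% dropout.
- Its assumptions: "we assume a mean reduction of 8.2 ± 7.0 points in the active control group, 12.4 ± 6.8 points in the low-dose group". For the high dose the assumed mean is 12.9, with SD 6.6.
- The abstract puts the question for the product as a whole: "This study aims to evaluate the efficacy and safety of PABG in children with TD".
- Section 4.1 plans an ANCOVA with least-squares mean differences between groups. Sections 2.7, 3.1, 4, 4.1 and 4.2 mention no contrast of the two PABG arms together against control. Dose-response is exploratory (sections 2.1 and 2.7) or descriptive (section 5.1).

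**The concern.** When two treatments are each tested against one shared control, the control arm enters the variance of both tests. Here it has 30 of 150 children, so its sampling error dominates both contrasts, and adding children to the dose arms does little to reduce it.

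The plan also leaves information unused. It assumes the two doses differ by only 0.5 points, yet each estimate against control uses only 60 of the 120 PABG children. A reader who wants to know how PABG compares with the 5% control on average must combine two correlated and less precise estimates.

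At stake are a realistic statement of the chance of success, and a more precise overall estimate from data the trial will already hold.

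**Working it through.** **Inputs (section 2.7).** Control: mean reduction 8.2, SD 7.0. Low dose: 12.4, SD 6.8 (difference 4.2). High dose: 12.9, SD 6.6 (difference 4.7). Two-sided alpha 0.025 per test, 15% dropout. Evaluable children at 60/60/30: 51/51/25.5.

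**Step 1: the plan's own figure.** With two per dose arm for each control, n_control = (z_alpha/2 + z_power)² × (SD_dose²/2 + SD_control²) / difference², and (2.241 + 0.842)² = 9.505.
- Low dose: 9.505 × (23.12 + 49) / 17.64 = 38.9, so 39:78:78 = 195 evaluable, about 230 randomised.
- High dose: 9.505 × (21.78 + 49) / 22.09 = 30.5, so 31:62:62 = 155 evaluable, about 185 randomised.

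The stated 150 is not reproduced. About 150 appears only with the high-dose effect and alpha 0.05 (pooled t: 125 evaluable, 125/0.85 = 147).

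**Step 2: variance factor of each primary contrast.**
- 60/60/30: 1/60 + 1/30 = 0.050.
- 50/50/50: 1/50 + 1/50 = 0.040.

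The planned ratio gives 25% more variance at the same total.

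**Step 3: power after dropout** (noncentral t, alpha 0.025; ranges run from the unequal-variance to the pooled-variance form).

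| Comparison | 60/60/30 | 50/50/50 | Loss |
|---|---|---|---|
| Low dose vs control | 57.5-59.4% | 69.9% | 10.5-12.4 points |
| High dose vs control | 69.3-72.2% | 81.5% | 9.3-12.2 points |

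With all 150 analysed, 60/60/30 gives 65.8-67.5% and 77.3-79.8%, still short of 80%.

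**Step 4: the average-dose contrast in the unchanged design.** The estimate is (low + high)/2 − control, with expected value (4.2 + 4.7)/2 = 4.45.
- SE, average contrast: √(0.25×6.8²/51 + 0.25×6.6²/51 + 7.0²/25.5) = √2.362 = 1.54.
- SE, low dose: √(6.8²/51 + 7.0²/25.5) = √2.828 = 1.68.
- SE, high dose: √(6.6²/51 + 7.0²/25.5) = √2.776 = 1.67.

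The standard error falls by 8-9%. With one common residual variance, as in ANCOVA, the ratio is √[(0.5/51 + 1/25.5)/(1/51 + 1/25.5)] = 0.91, which is the same gain.

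**Step 5: power at matched alpha** (average contrast with N − 3 = 124.5 degrees of freedom).

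| Alpha | Average contrast | High dose | Low dose |
|---|---|---|---|
| 0.025 | 73.4% | 69.3-72.2% | 57.5-59.4% |
| 0.05 | 81.9% | 78.9-81.1% | 68.7-70.2% |

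The gain is about 1-4 points over the high-dose test and about 12-16 over the low-dose test. Under unequal-variance degrees of freedom (about 36.5) the average contrast has 71% and 80%.

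**Step 6: could covariate adjustment restore 80%?** No correlation is given. If the covariates correlate ρ with the change score, variance shrinks by 1 − ρ². By the normal approximation, 80% power needs an SE of 4.2/3.083 = 1.362 (low) or 4.7/3.083 = 1.524 (high). Then 1 − ρ² = 1.362²/2.828 = 0.656, so ρ is about 0.59; and 1.524²/2.776 = 0.837, so ρ is about 0.40. Section 2.7 claims no such gain.

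**The case against.** The allocation ratio is a legitimate design choice. Safety is an aim beside efficacy, the trial calls itself exploratory and dose-finding, and 2:2:1 gives 120 PABG exposures and keeps fewer children on a 5% preparation not meant to have a pharmacological effect. A condensed article need not print its reasons. This stands: the ratio is not an error, and the absence of a stated rationale is not the point.

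A reader might infer that 2:2:1 must have been chosen for a comparison of all PABG children with control. The arithmetic does not support that. Pooling makes a 120-to-30 split with variance factor 1/120 + 1/30 = 0.0417, against 1/100 + 1/50 = 0.0300 under 50/50/50. The ratio costs the pooled comparison 39% more variance, worse than the 25% for each dose; pooled power at 0.05 is 82% under 60/60/30 and 93% under 50/50/50.

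A reader might also infer that the remaining children should be switched to 1:1:1. Recruitment opened on 15 September 2025 and is due to close on 31 December 2026. If half were already randomised (an assumption), the result would be 55/55/40, with about 66% and 77-79% power. That gain of roughly 6-8 points would need a ratio change in a blinded trial with six strata and a period term, and would move up to 20 children from PABG to control. Even a full 1:1:1 leaves the low dose near 70%.

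Setting 82% for the average contrast beside 58-72% for the dose tests would mix alphas, and most of the apparent gain over the high-dose test would come from that. Testing the contrast at 0.05 on top of two tests at 0.025 would also exceed the error budget. Both objections hold, which is why the contrast is proposed as an estimate only.

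Finally, an unseen SAP may already contain it. If so, only the power statement remains to be changed.

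**Conclusion.** The point holds as one of efficiency and of an overstated power claim. The trial's validity is not in question.

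- Both primary tests share the 30-child arm. Relative to 1:1:1 at 150, each loses about 9-12 points after dropout.
- On the inputs of section 2.7, 60/60/30 delivers about 58-59% and 69-72%, not 80%. Most of the shortfall for the low dose is not due to the ratio, because 150 does not follow from the stated inputs in the first place.
- No planned contrast *with control* uses all 120 PABG children. It would be too broad to say that no analysis does, since the exploratory look at dose-response draws on both arms.
- One supportive contrast gives an average PABG estimate with an 8-9% smaller standard error. That is a modest gain, worth having because it is almost free.

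These figures assume the stated means and SDs, 15% loss in every arm with no information recovered by imputation, and no gain from covariates. Covariate adjustment would raise power under either ratio, but it would not alter the 0.050 against 0.040 comparison.

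**What to change.** **Section 4.1.** Add one prespecified contrast to the primary ANCOVA, with coefficients ½, ½ and −1 for low dose, high dose and control. Suggested text: *As a supportive estimate of the average PABG effect, the mean of the two PABG least-squares means minus the control least-squares mean will be reported with a 95% CI. It lies outside the Bonferroni family, and no confirmatory claim will rest on it.* Leave the two dose comparisons and their alpha as they are.

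**Section 2.7.** Restate the power for 60/60/30 on the stated inputs (about 58-59% and 69-72% after dropout). If the 80% relied on a covariate correlation or another alpha, say so and give it.

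**Cost.** One contrast statement and one revised power statement, both settled before unblinding; no extra children and no change to the randomisation list. The average is less informative if the two doses differ much, so the separate dose estimates must be shown beside it.

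**Optional.** Changing the ratio for children not yet randomised is for the sponsor to weigh against PABG safety data, exposure to the 5% control and the burden of an amendment. This point does not require it.
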